#### Biobanking

Blood samples for inflammatory and coagulation pathway activation will be collected prior to cannulation, as well as at 1, 12, and 24 hours post commencement of ECMO. These samples will be frozen using standard operating procedures and batch tested.

## Results

### Study Outcomes

The NECTAR trial is a pilot RCT; hence, it will focus on safety and feasibility outcomes in addition to exploring efficacy outcomes as described in Textbox 1. This work was supported by grants from the Children’s Hospital Foundation, Brisbane, Australia, and by a grant from the Thrombosis and Hemostasis Society of Australia. The results are expected to be published at the end of 2023 or early 2024.

Main study outcomes and secondary analyses for the Nitric Oxide on Extracorporeal Membrane Oxygenation in Neonates and Children (NECTAR) trial.
**Main study outcomes**
Feasibility outcomesMonthly recruitment rateRandomized to screened patient ratioCompliance with the study protocol (with particular focus on the timing of the initiation of nitric oxide (NO) and the maintenance of NO for the duration of the study)Safety outcomesFailure rate of gas deliveryCarbon dioxide control of patientsMethemoglobin levelsEfficacy outcomesHost systemic inflammation levels at 1, 12, and 24 hoursCoagulation system activation and consumptionClotting and bleeding complicationsRate of clotting and bleeding events
**Secondary outcomes**
Survival without extracorporeal membrane oxygenation (ECMO), censored at 30 and 90 days post randomization. Patients dying within 30 and 90 days of presentation will be considered as 0 days, to account for the competing effect of mortality on ECMO-free survival.Survival free of pediatric intensive care unit (PICU; censored at 30 and 90 days)Hospital length of stay post randomizationMedian daily blood product usageComplement system activationChild neurodevelopment, function, and quality of life at 6 and 12 months, as measured by:Ages and Stages Questionnaire (<5 years of age) OR Strength and Difficulties Questionnaire (>5 years of age)Pediatric Quality of Life InventoryPediatric Emotional Distress Scale (2-5 years) OR Children’s Revised Impact of Events Scale (>5 years)Behavior Rating Index of Executive Functioning – Preschool (2-5 years) OR Behavior Rating Index of Executive Functioning – 2 (>5 years)Vineland Adaptive Behavior ScaleParent functioning at 6 and 12 months, as measured by:Parenting Stress Index – Short FormKessler-6Primary Caregiver – Post Traumatic Stress Disorder Scale

### Feasibility Outcomes

The focus will be on the monthly recruitment rate, the randomized to screened patient ratio, and protocol adherence, that is, how many blood collection points, computer tomography scans of oxygenators, and daily indirect oxygenator clot measurements (by extracorporeal life support assessment monitor) were completed.

### Safety Outcomes

There will be a focus on sweep gas delivery failure related to NO administration. Specifically, an arterial oxygen saturation of less than 80 due to a sweep gas interruption related to NO administration or carbon dioxide control outside of 30 to 50 mm Hg due to NO administration will be recorded as a safety event. The methemoglobin (MetHb) levels during the time of ECMO will be measured, and events above 3% related to NO administration will be noted.

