**Methods:**

The Nitric Oxide on Extracorporeal Membrane Oxygenation in Neonates and Children (NECTAR) trial is an open-label, parallel-group, pilot randomized controlled trial to be conducted at a single center. Fifty patients who require ECMO support will be randomly assigned to receive either NO mixed into the sweep gas of the ECMO system at 20 ppm for the duration of ECMO or standard care (no NO) in a 1:1 ratio, with stratification by support type (veno-venous vs veno-arterial ECMO).

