**Results:**

Outcome measures will focus on feasibility (recruitment rate and consent rate, and successful inflammatory marker measurements), the safety of the intervention (oxygenation and carbon dioxide control within defined parameters and methemoglobin levels), and proxy markers of efficacy (assessment of cytokines, chemokines, and coagulation factors to assess the impact of NO on host inflammation and coagulation cascade activation, clotting of ECMO components, including computer tomography scanning of oxygenators for clot assessments), bleeding complications, as well as total blood product use. Survival without ECMO and the length of stay in the pediatric intensive care unit (PICU) are clinically relevant efficacy outcomes. Long-term outcomes include neurodevelopmental assessments (Ages and Stages Questionnaire, Strength and Difficulties Questionnaire, and others) and quality of life (Pediatric Quality of Life Inventory and others) measured at 6 and 12 months post ECMO cannulation. Analyses will be conducted on an intention-to-treat basis.

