### Interventions

Infants and children will be randomly assigned to receive either NO or standard care. Those allocated to the intervention (NO) will receive 20 ppm of NO mixed into the sweep gas running into the oxygenator during their ECMO run. The NO concentration will be maintained at 20 ppm using a NO delivery system (Sokinox, Maquet), or a similar device. Continuous sampling of NO and NO_2_ concentrations is performed by the Sokinox machine by gas aspiration after the NO injection site. Patients allocated to the standard study arm will receive the standard oxygen-air mix in the ECMO oxygenator as per institutional practice and protocol.

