### Sample Size

The NECTAR trial is a pilot RCT with the main focus on feasibility, safety, and exploration of efficacy. A sample size of 50 patients has been chosen in line with the recommendations for pilot studies that anticipate a medium effect size for a continuous primary outcome for the main trial [17].

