### Adverse Events

Given the severity of the underlying disease leading to the requirement for ECMO, patients are expected to have a high rate of adverse events unrelated to the study intervention. Events that are in the expected range of adverse events during standard treatment will therefore not be reported as related to the study intervention, as previously described [19]. Adverse events that are likely related to the study intervention will be reported. Adverse events likely related to NO delivery during ECMO support, such as failure to deliver sweep gas to the oxygenator, poor patient carbon dioxide control due to sweep gas failure, and increased MetHb (MetHb >3%) at any of the blood gas sampling points, will be reported [11,12]. Death will be reported as an adverse event and will be assessed as to whether it may be related to the study intervention. The study team, together with the treating physician, will assess each patient’s case and make an initial assessment of whether death occurred due to the intervention. The final assessment is to be confirmed with the DSMB.

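### The saturation, CO2 and MetHb >3% safety events count only when attributed to NO, so the rates of these defined events cannot be compared between arms

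*Protocol article*

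**What the plan says.** The Safety Outcomes section defines three events, each with a causal condition:

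- Oxygenation: "an arterial oxygen saturation of less than 80 due to a sweep gas interruption related to NO administration".
- Carbon dioxide: "carbon dioxide control outside of 30 to 50 mm Hg due to NO administration will be recorded as a safety event".
- Methemoglobin: levels are measured throughout ECMO without any condition, but for the threshold event "events above 3% related to NO administration will be noted".

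Two other places describe the same safety domain without attribution. The Results paragraph of the abstract gives it as "oxygenation and carbon dioxide control within defined parameters and methemoglobin levels". Textbox 1, under Study Outcomes, lists gas delivery failure rate, CO2 control and MetHb levels as main safety outcomes and ties none of them to NO.

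The comparator is described in the abstract as "standard care (no NO) in a 1:1 ratio". The Interventions section confirms it: "Patients allocated to the standard study arm will receive the standard oxygen-air mix in the ECMO oxygenator". The section on blinding says that blinding is not possible.

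**The concern.** Safety is one of the stated purposes of this pilot, and the results are meant to inform a definitive trial. Low saturation and CO2 excursions can occur in any child on ECMO, and the Adverse Events section itself expects a high rate of events unrelated to the intervention. In that setting individual attribution is least reliable, and a concurrent control arm is most useful as the source of the background rate.

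An event definition that requires NO causation discards that background rate. The control count is fixed at zero as far as the study gas is concerned, whatever actually happens to those children. The NO-arm count becomes the true count multiplied by the share that someone who knows the allocation ascribes to NO. The resulting contrast could suggest harm where there is none, or show nothing where there is an excess. The article also leaves two incompatible versions of the safety outcomes, which would give different counts from the same data.

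**Working it through.** **Inputs from the article.** The total is 50 (Sample Size: "A sample size of 50 patients has been chosen in line with the recommendations for pilot studies that anticipate a medium effect size"). With 1:1 allocation this is 50/2 = 25 per arm. The 50 rests on an outside recommendation and cannot be re-derived from the article; this point does not depend on it. The Analysis Plan sets the significance level at .05 and names a test of two proportions for binary data. The article does not say that the safety events will be tested between arms, so the test serves here only to gauge the distortion.

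**Assumptions (the article gives no event rates).** A true all-cause proportion p of children with at least one event, equal in both arms, from 10% to 50%; and a share s of NO-arm events attributed to NO.

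**Step 1: the structure.** Under the Safety Outcomes definitions the control count is 0 of 25 for every p. The NO-arm count X is binomial with n = 25 and probability p × s. At p = 0.30 the expected NO-arm count is 25 × 0.30 × s, which is 0, 1.88, 3.75 and 7.5 for s = 0, 0.25, 0.50 and 1. The expected difference between arms is therefore set by s, although NO has no effect in this example.

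**Step 2: how many attributed events look significant against 0/25.** With pooled proportion x/50, z = (x/25) / √[(x/50)(1 − x/50)(2/25)].

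- x = 3: z = 0.12/0.0672 = 1.79, p = 0.074.
- x = 4: z = 0.16/0.0767 = 2.09, p = 0.037.
- Fisher's exact test: x = 5 gives p = 0.0502 and x = 6 gives p = 0.022.

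The cut-offs are therefore 4 attributed events (z test) and 6 (Fisher).

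**Step 3: chance of p<0.05 when NO has no effect.** This is P(X ≥ 4) for the z test and P(X ≥ 6) for Fisher.

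| True rate, both arms | s = 25% (z / Fisher) | s = 50% (z / Fisher) | s = 100% (z / Fisher) | All-cause count in both arms (z / Fisher) |
|---|---|---|---|---|
| 10% | 0.003 / 0.000 | 0.034 / 0.001 | 0.236 / 0.033 | 0.049 / 0.009 |
| 20% | 0.034 / 0.001 | 0.236 / 0.033 | 0.766 / 0.383 | 0.055 / 0.022 |
| 30% | 0.113 / 0.009 | 0.529 / 0.162 | 0.967 / 0.807 | 0.054 / 0.023 |
| 50% | 0.382 / 0.083 | 0.904 / 0.622 | 1.000 / 0.998 | 0.065 / 0.033 |

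All-cause counting stays near or below the nominal level. Attributed counting ranges from almost 0 to almost 1, depending on s.

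**Step 4: the opposite error.** Assume 10/25 control and 15/25 NO children have a CO2 excursion, a difference of 60% − 40% = 20 points. If 0 to 25% of the NO-arm events are attributed, the recorded result is 0 to 3.75 (about 4) of 25 against 0 of 25. With s = 0 the excess disappears completely.

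**Step 5: what all-cause counting would deliver.** For the same example, 0.20 ± 1.96 × √(0.4 × 0.6/25 + 0.6 × 0.4/25) = 0.20 ± 0.27, so the 95% CI runs from about −7 to 47 points. Power for 20% versus 40% with 25 per arm is about 0.34. The comparison becomes valid but remains imprecise.

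**The case against.** A reader might infer that the randomized comparison of the main safety outcomes is lost altogether. The article does not support that. MetHb levels are measured without a causal condition, and Textbox 1 lists all three safety outcomes unattributed. Mortality at 30 and 90 days, bleeding and clotting, seizures, renal function and hemolysis carry no attribution either. The Monitoring section has all severe adverse events recorded, and an independent DSMB monitors adverse events.

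A reader might also infer from the Adverse Events section that an excess of common events would be filtered out, because "Events that are in the expected range of adverse events during standard treatment will therefore not be reported as related to the study intervention". That sentence governs only what is reported as related; it does not say that such events go unrecorded. The same section then names sweep-gas failure, the resulting poor CO2 control and MetHb above 3% as events to be reported, although as events likely related to NO delivery.

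Three further points have weight. First, gas delivery failure caused by the NO equipment is a hazard specific to that arm, and its absolute rate there is a legitimate pilot quantity. Second, the article does not say who attributes these events; it describes an assessment process only for deaths. Third, the control zero assumes that no control child receives NO by another route, on which the article is silent.

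These points limit the reach of the concern but do not remove it. A device-failure rate in one arm does not justify a causal condition on CO2 control. Whoever attributes the events, the trial is open label. The mismatch between Safety Outcomes and both the abstract and Textbox 1 remains.

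**Conclusion.** The point holds for the defined events: saturation below 80, CO2 outside 30 to 50 mm Hg, and MetHb above 3%. As written in Safety Outcomes, their counts are zero in the control arm through the study gas and depend on judgement in the NO arm, so they give no valid between-arm contrast. They also conflict with the unattributed outcomes in the abstract and Textbox 1, and the passages must be reconciled. The comparison of MetHb levels, mortality and the other unattributed outcomes is intact.

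The structural zero follows from the wording, provided that controls receive no NO by another route. The probabilities are illustrations that rest on assumed event rates and attribution shares. One figure should not be read as a measure of this defect: zero events in 25 children leaves an exact 95% upper limit of 1 − 0.025^(1/25) = 13.7%, but that reflects the arm size and would be the same under any definition. No judgement is made here on the clinical thresholds.

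**What to change.** Reconcile Safety Outcomes with the abstract and Textbox 1 as follows.

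- Count every crossing of the existing saturation, CO2 and MetHb thresholds, and every sweep-gas interruption, by the same criteria in both arms regardless of cause. Use the blood-gas and physiological values recorded on schedule.
- Report by arm the number of patients with at least one event and the events per ECMO day, with confidence intervals for the difference.
- Keep NO-relatedness as a separate descriptive field, including gas delivery failure due to the NO device in the NO arm.
- Leave the thresholds as they are.

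**Cost.** The change is mainly one of wording and data extraction. Recruitment began in August 2020, so extraction for children already enrolled may have to be retrospective. The Data Collection section schedules physiological and blood parameters without naming CO2 or saturation; the Adverse Events section does refer to blood gas sampling points, so the values are probably available, but this should be confirmed. Values at 1, 12 and 24 hours and daily thereafter may miss transient desaturations, and a brief interruption of sweep gas would need its own record. The change removes the attribution bias; it does not improve the low precision at about 25 per arm.

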### Efficacy Outcomes

Host inflammation and complement components will be assessed before cannulation and at 1, 12, and 24 hours post cannulation by determining serum concentrations of C-reactive protein, procalcitonin, IL-1b, IL-6, IL-8, IL-10, and TNF-*α*. At the same time points, coagulation system activation will be assessed by measuring the international normalized ratio (INR), prothrombin time (PT), activated partial thromboplastin time (APTT), thromboelastography (TEG), antithrombin, soluble CD40L, P-selectin, platelet factor 4 levels, and ADAMTS13 release (see Textbox 2). A single measurement of Von Willebrand factor at initiation followed by daily measurements will be performed. After the initial 24 hours, further daily laboratory testing will include D-Dimers, TEG, INR, PT, APTT, anti Xa and activated clotting time (by TEG), and plasma-free hemoglobin. Clotting and bleeding complications and the rate of clotting and bleeding events will be measured. Clotting events are defined as the need to change ECMO circuit componentry due to high transmembrane pressures, high D-Dimers, or high free plasma hemoglobin. Bleeding rates will be measured by both the amount of bleeding per day as well as the daily requirement for blood product administration.

Coagulation, inflammation, and complement system measurements.Coagulation system measurementsChange in granule (soluble CD40 ligand and P-selectin) and chemokine (platelet factor 4) levels released by activated plateletsADAMTS13 releaseChange in van Willebrand factor concentrations during and after the extracorporeal membrane oxygenation (ECMO) runChanges in inflammatory and complement system activationChange in C-reactive protein, procalcitonin, interleukin (IL)-1b, IL-6, IL-8, IL-10, and tumor necrosis factor *α* (inflammatory mediators) levels; Complement (C)1q, Complement Factor B, Complement Factor H, C5a, C9, and Mannose-Binding Lectin (classic and alternate complement pathways); and C3, C3 and CH50.

### Secondary Clinical Outcomes

The secondary clinical outcomes include mortality at 30 and 90 days. ECMO-free and PICU-free survival censored at 30 and 90 days post randomization, length of stay at the hospital post randomization, average daily blood product usage, complement system activation with measurements of complement (C)1q, C5a, C9, C3, C4, complement factor B, complement factor H, and Mannose-binding Lectin, as well as neurodevelopmental function and quality of life at 6 and 12 months, will be considered (Textbox 3).

Subanalyses for the Nitric Oxide on Extracorporeal Membrane Oxygenation in Neonates and Children (NECTAR) trial.Cardiac, respiratory, and extracorporeal membrane oxygenation–assisted cardiopulmonary resuscitation outcomes (proportions alive at 30 and 90 days for each group)Circuit duration (time to decannulation or time to circuit change) per treatment groupRenal function measured as creatinine and urine output changes during extracorporeal membrane oxygenation (ECMO) per treatment groupRenal replacement treatment on ECMO (type of renal replacement therapy, duration of slow continuous ultrafiltration, type of filter, and duration of filter viability)Incidence of seizures diagnosed during ECMO or up to 48 hours after decannulationTransmembrane oxygenator pressure assessment every 24 hoursOxygenator clot volume as assessed by the extracorporeal life support assessment monitorOxygenator clot volume (by computer tomography imaging)Hemolysis (plasma-free hemoglobin) per treatment groupMean daily heparin dose per kg required to meet target anticoagulation per treatment group

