### Statistical Analysis Plan

#### Analysis Plan

Descriptive statistics will be used to report the baseline characteristics of the total study cohort and each subgroup. The primary efficacy outcome measure investigating days free of ECMO will be analyzed using quantile regression incorporating treatment group and VA or VV support (stratification variable) as fixed effects, with the treatment group effect estimate and 95% CI reported (assuming the data is abnormally distributed). Exploratory subgroup analysis by cardiac, respiratory, and ECMO-assisted cardiopulmonary resuscitation support will be performed. Analysis of secondary outcomes includes comparisons of measurements and proportions, with confidence intervals of differences as the major method of presentation. The primary analysis will be by intention-to-treat. If appropriate, per-protocol analyses will be performed as well and compared to the intention-to-treat. Statistical significance will be set at the .05 level and no adjustment for multiple comparisons will be made, noting the exploratory nature of the analysis. CIs will be generated using quantile regression for abnormally distributed continuous data, a 2-sided *t* test for normally distributed data, and a test of 2 proportions for binary data.

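### Hospital length of stay is compared as a raw duration with no stated rule for deaths, so it can favour the arm with more deaths

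*Protocol article*

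**What the plan says.** Hospital stay counted from randomization appears twice as a plain duration: under Secondary outcomes in Textbox 1, and under Secondary Clinical Outcomes as "length of stay at the hospital post randomization, average daily blood product usage". Neither place gives a time horizon or says how an in-hospital death is counted.

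The same Textbox list does give a death rule for ECMO-free survival. Patients who die within the window "will be considered as 0 days, to account for the competing effect of mortality on ECMO-free survival". The sentence names that outcome only. The PICU outcome in the list is also framed as survival free of PICU, not as a raw stay.

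On method, the Analysis Plan section states: "Analysis of secondary outcomes includes comparisons of measurements and proportions, with confidence intervals of differences as the major method of presentation". It adds that "CIs will be generated using quantile regression for abnormally distributed continuous data", with a 2-sided t test for normally distributed data. It also says "The primary analysis will be by intention-to-treat" and "Statistical significance will be set at the .05 level and no adjustment for multiple comparisons will be made".

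The abstract words the PICU outcome differently from the lists: "Survival without ECMO and the length of stay in the pediatric intensive care unit (PICU) are clinically relevant efficacy outcomes".

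**The concern.** A raw stay ends at discharge or at death, whichever comes first. Under an intention-to-treat comparison with no death rule, a child who dies on day 3 contributes a 3-day stay, which ranks among the most favourable values. Neither quantile regression nor a t test corrects for this.

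The article describes the mortality risk of these children as very high, so deaths will make up a material share of the data. If NO changes survival, raw stay can move in the opposite direction to ECMO-free days in the same report, although the recovery of survivors is unchanged. The pilot is meant to inform a definitive trial, so an outcome that can point the wrong way could be carried forward.

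**Working it through.** **Inputs from the article.** 50 patients, 1:1, so 50/2 = 25 per arm; two-sided .05 level. It gives no mortality rate and no length of stay, so there is no planned figure for this outcome to reproduce.

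**Assumptions.** Stays are log-normal with log-SD 0.7. The median is s days in survivors and d days in deaths, the same in both arms. Only the mortality p differs between arms, so NO has no effect on survivors' stay.

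**Formula.** The median raw stay m in an arm solves

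p·Φ(ln(m/d)/0.7) + (1−p)·Φ(ln(m/s)/0.7) = 0.5.

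Example with s = 40, d = 10:
- p = 0.4: m = 24.2, since 0.4×0.896 + 0.6×0.236 = 0.358 + 0.142 = 0.500.
- p = 0.2: m = 32.7, since 0.2×0.955 + 0.8×0.386 = 0.191 + 0.309 = 0.500.
- Difference: 32.7 − 24.2 = +8.5 days. The arm with half the deaths appears to stay longer.

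**Across assumed stays, mortality 40% (control) versus 20% (NO).** The last column is the share of simulated trials, 25 per arm, in which a rank test gave p < .05 in either direction. The rank test stands in for the planned median comparison.

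| s / d (days) | Control median | NO median | Shift | Rank test p < .05 |
|---|---|---|---|---|
| 25 / 15 | 20.4 | 22.7 | +2.2 | about 7% |
| 35 / 20 | 28.1 | 31.5 | +3.4 | about 7% |
| 25 / 10 | 17.6 | 21.3 | +3.7 | 11% |
| 40 / 20 | 30.5 | 35.2 | +4.7 | 9% |
| 35 / 10 | 22.0 | 28.9 | +6.9 | 15–16% |
| 40 / 10 | 24.2 | 32.7 | +8.5 | 17% |
| 60 / 15 | 36.2 | 49.0 | +12.8 | 16% |
| 40 / 40 | 40.0 | 40.0 | 0 | 5% |

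**Other contrasts.**
- Harm, 40% versus 60%, stays 40/10: the NO median falls by about 7.6 days, so the arm with more deaths looks better. The stay is significantly shorter with NO in 16% of trials.
- Smaller difference, 40% versus 30%: +3.5 days for 35/10 (rejection about 7%) and +1.7 days for 35/20 (about 5%).
- Equal mortality, 40% versus 40%: no shift.

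**Same model with the death rule applied** (90 minus stay, floored at 0; deaths = 0), s = 40, d = 10:
- 40% versus 20%: mean difference +8.8 days in favour of NO; significantly better in 19% of trials, worse in 0.1%.
- 40% versus 60%: mean difference −8.9 days; significantly worse in about 22%, better in 0%.

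The direction now follows survival.

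**The case against.** The strongest objection is that this is an omission and not a stated error. The article never says that deaths enter as short stays. Intention-to-treat fixes who is analysed, not how a death is scored, and the full protocol or analysis plan may hold a rule. That stands in part: the absence of a rule can be asserted only of this article. It does not remove the point. How deaths count is part of the definition of a duration outcome, and the article supplies that definition for a neighbouring outcome, giving the reason "to account for the competing effect of mortality on ECMO-free survival". Reading the outcome as survivors only would avoid short stays from deaths, but it would compare groups selected after randomization.

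Other objections stand as limits. Observed stay is a legitimate measure of bed use. Mortality at 30 and 90 days is reported alongside, so a reader could see the deaths. The outcome is secondary, unadjusted and exploratory, in a pilot that states it is not powered for clinical outcomes.

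Three stronger readings might be inferred, and the documents do not support them.
- A life-saving effect would necessarily show as a longer stay. It would not: the distortion needs both unequal mortality and deaths earlier than discharges, and most simulated trials show no significant difference.
- The rejection rates above are inflated type I errors. They are not, because in those scenarios the distributions of raw stay really differ. The trouble is what that difference means.
- Raw PICU stay is also a planned comparison. That wording is only in the abstract; the outcome lists specify PICU-free survival.

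**Conclusion.** The point holds, at modest severity. In this article hospital stay is a raw duration with no rule for deaths. Where deaths precede discharges and mortality differs, the comparison favours the arm with more deaths and can contradict ECMO-free days.

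The size is conditional. For an absolute mortality difference of 20 points (40% versus 20%), the median moves by about 2 to 13 days over the assumed stays. It moves less for a 10-point difference, and not at all with equal mortality or late deaths. These figures rest on assumed mortality, stay lengths and a log-normal shape, none of which the article provides. The direction depends only on the two conditions named.

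**What to change.** - In Textbox 1 and under Secondary Clinical Outcomes, replace hospital length of stay by days alive and out of hospital to day 90 after randomization, with deaths by day 90 scored as 0. This extends the rule already used for ECMO-free survival. Analyse it with the quantile regression already planned for ECMO-free days (treatment group and VA/VV stratum).
- Alternatively, analyse time to discharge alive with death as a competing event.
- Report raw stay descriptively only, separately for survivors and deaths.
- In the abstract, replace PICU length of stay by PICU-free survival, as in the outcome lists.

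One caution for the first option: if half or more of an arm scores 0, its median is 0 and a median difference says little. In the 60/15 scenario with 40% versus 60% mortality, both medians are 0 although the means differ by 6.1 days. Either name in advance a quantile that avoids this, or use the competing-event analysis.

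Cost: wording and analysis code only, with no extra patients or procedures. The death and discharge dates are already implied by the listed outcomes; counting to first discharge avoids collecting readmissions. The downside is that the new measure mixes mortality with duration and no longer describes bed use, which the descriptive report covers.
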